#### Secondary outcomes

Secondary outcomes will include: (1) rate of remission/recovery of depression (major depressive disorder or persistent depressive disorder) using the Structured Clinical Interview for DSM-5 (SCID-5) [31], (2) the Inventory of Depressive Symptomatology Self-Report (IDS-SR) [34, 35], (3) the Fear Questionnaire (FQ) [32], (4) the Multidimensional Scale of Perceived Social Support (MSPSS) [36], and (5) The brief version of the WHO Quality of Life (WHOQOL-BREF) [37].

#### Potential mediators and moderators

For potential moderators and mediators of the outcome, we will assess: (1) a Visual Analogue Scale (VAS) of mood (one-item mood scale) [38], (2) the Positive and Negative Affect Scale (PANAS) [39], (3) the Behavioral Activation for Depression Scale Short Form (BADS-SF) [40], (4) the Life-events scale [41], (5) history of depressive disorders (major depressive disorder and persistent depressive disorder) and trauma- and stressor-related disorders as assessed using the SCID-5 interview [31], and (6) our self-developed Childhood trauma.

#### Additional measures

For additional measures, since Indonesia is rich in cultural diversity, we will collect data on ethnic identity using the Multigroup Ethnic Identity Measure (MEIM) [42]. We will also examine sociodemographic characteristics (i.e. age, gender) and clinical information (i.e. depression attribution, psychiatric-related health care consumption) in each participant.

### Main study hypotheses

That participants receiving the GAF-ID will have a lower level of depression symptoms on the PHQ-9 [30] at the main time point of measuring effectiveness after 10 weeks from baseline (post intervention) compared to participants in the PE group. The lower level of depression symptoms measured using the same tool is also expected to present in the GAF-ID arm relative to the PE arm at the 3-month and 6-month follow-ups.

Furthermore, the incidence of major depressive disorder and persistent depressive disorder measured using the SCID-5 [31] is expected to be lower in the GAF-ID group compared to the PE group at post intervention and follow-ups, along with lower depressive symptoms measured using the IDS-SR [34, 35], lower anxiety levels measured using the FQ [32], higher perceived social support as measured by the MSPSS [36], and higher quality of life as measured by WHOQOL-BREF [37].

All potential moderators are hypothesized to predict outcome measures, whereas potential mediators are supposed to underlie the reduction in depression symptoms. Moreover, ethnic identity, sociodemographic characteristics and clinical information will be examined as additional data.

### Power calculation

Psychoeducation has been used as the comparator in some online and non-online depression treatment trials with effect sizes ranging from 0.03 to 0.85 [43–45]. Given the fact that we plan to perform this study in a unique target population (a LMIC), the statistical power was calculated to estimate a rather conservative small to medium effect size. The power is calculated to detect differences between two independent groups, in a two-sided test at alpha = 0.05 and a power of (1 − beta) = 0.80, for an effect size of 0.35 (small to medium effect size). Based on these parameters, we will need a sample of 260 participants. To compensate for the expected 20 % attrition we will need to include and randomize 312 participants at baseline.

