**Methods:**

An Internet-based behavioral activation treatment, with support by lay counselors who will provide online feedback on the assignments and supportive phone contact to encourage participants to work in the program (Guided Act and Feel Indonesia/GAF-ID), is compared to an online-delivered minimal psychoeducation without any support (psychoeducation/PE). Initial assessment for inclusion is based on a Patient Health Questionnaire-9 (PHQ-9) score of at least 10 and meeting criteria for major depressive disorder or persistent depressive disorder as assessed using the Structured Clinical Interview for DSM-5 (SCID-5). Participants with depression (*N* = 312) will be recruited and randomly assigned to GAF-ID or PE. Overall assessments will be done at baseline, post intervention (10 weeks from baseline) and follow-ups (3 months and 6 months from baseline). The primary outcome is the reduction of depression symptoms as measured by the PHQ-9 after 10 weeks from baseline.

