### Participants

#### Recruitment

We aim to recruit 312 participants for this study from the community through advertisements, via the mass media (banners placed in various related websites and places, newspapers and magazines), social media (online groups, pages, and forums related to mental health issues), and referral from mental health institutions or mental health professionals. The potential participants will be able to access information regarding the trial on our study website: www.actandfeel.com and they can fill in the Patient Health Questionnaire-9 (PHQ-9) [30] for screening purpose on a linked online survey system, the Qualtrics website. If they have scores of at least 10, we will make sure that they understand all aspects of the trial and invite them or their legal guardian to fill in a written informed consent to provide their sociodemographic information and join a clinical interview using the Structured Clinical Interview for the *Diagnostic and Statistical Manual of Mental Disorders*, *fifth edition* (DSM-5) (SCID-5) [31] through a phone call. If they meet all inclusion and none of the exclusion criteria for the study, they are eligible to join the study. The participants will also be informed that each of them who is participating until the last follow-up assessment (6 months from baseline) will receive a monetary incentive, irrelevant of the group to which they belong.

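### The attrition allowance multiplies 260 by 1.2 instead of dividing by 0.80, so 312 randomised leave about 250 with week-10 data at the plan's own 20% attrition (about 79% power, not 80%)

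*Protocol article*

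**What the plan says.** All the inputs stand in the Power calculation section of the protocol article. The test is a simple comparison of the arms: "The power is calculated to detect differences between two independent groups", "in a two-sided test at alpha = 0.05" and with "a power of (1 − beta) = 0.80". The standardised effect is 0.35. The section concludes: "Based on these parameters, we will need a sample of 260 participants". It then allows for an expected 20% "attrition we will need to include and randomize 312 participants at baseline".

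The same target appears twice more. Under Recruitment: "We aim to recruit 312 participants for this study from the community". In the Methods part of the abstract, 312 participants with depression "will be recruited and randomly assigned to GAF-ID or PE". Neither place gives another derivation of 312.

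**The concern.** The 260 is the number that the stated test needs in the analysis. The 312 is meant to be large enough that 260 remain after 20% are lost. Adding 20% of 260 does not achieve this, because the loss is a fraction of the larger number randomised, not of the 260.

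The four stated figures (effect size 0.35, power 0.80, attrition 20%, 312 randomised) therefore cannot all hold under the stated method. What is at stake is a headline design figure that does not follow from its own inputs and errs on the unfavourable side. The 260 leaves almost no slack to absorb the error, since its power is 0.803.

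**Working it through.** **Inputs** (all from Power calculation, except allocation): two independent groups; two-sided alpha 0.05; power 0.80; standardised effect d = 0.35; requirement 260; attrition 20%; randomised 312. Allocation is taken as 1:1. The article describes two arms but states no ratio, so this is an assumption.

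**Step 1: reproduce 260.**
- Normal approximation: n per arm = 2 × (1.960 + 0.842)² / 0.35² = 128.1, so 129 per arm and 258 in total.
- Two-sample t-test: n per arm = 129.1, so 130 per arm and **260** in total.

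The plan's 260 is reproduced exactly by the t-test.

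**Step 2: reproduce 312.**
- 260 × (1 + 0.20) = **312** exactly. This is evidently the step taken.
- 260 / (1 − 0.20) = **325**, or 326 for two equal arms of 163. This is the number that leaves 260 after 20% are lost.
- Rounding does not explain the gap: starting from 258, the corrected figure is 258 / 0.80 = 322.5, so 323.

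**Step 3: what 312 leaves.**
- 312 × 0.80 = 249.6, so about 250 participants with week-10 data (124.8 per arm), some 10 fewer than 260.
- Attrition at which 312 leaves 260: (312 − 260) / 312 = 52 / 312 = 16.7%.
- Shortfall in randomised participants: 325 − 312 = 13 (14 with equal arms), and 13 / 325 = 4%.

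**Step 4: power for d = 0.35, two-sided alpha 0.05.**

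| Participants with week-10 data | Power, t-test | Power, normal approximation |
|---|---|---|
| 249.6 | 0.786 | 0.790 |
| 250 | 0.787 | 0.790 |
| 258 | 0.800 | 0.803 |
| 260 | 0.803 | 0.806 |

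With 124.8 per arm, the effect detectable with 80% power in the t-test is 0.356, against the 0.35 planned.

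**The case against.** **The analysis is not a t-test on those who reach week 10.** This is the strongest point on the other side. The Primary analysis section plans an intention-to-treat linear mixed model that uses all available data. Table 1 schedules the PHQ-9 at baseline and at weeks 2, 4, 6, 8 and 10, so many who miss week 10 may still contribute. The gain depends on correlations that the article does not give. As an illustration, take a baseline-adjusted comparison of the week-10 score with 124.8 per arm, where the effective effect size is 0.35 / √(1 − r²) for an assumed baseline-to-week-10 correlation r. Power is then 0.786 at r = 0, 0.803 at r = 0.2, 0.823 at r = 0.3 and 0.889 at r = 0.5. A correlation of about 0.19 restores 80%. Recovery is not assured: an unadjusted change-score contrast gains only if r exceeds 0.5 and loses below that.

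This objection stands against any flat statement that the trial loses power. It does not rescue the sentence in the Power calculation section, which rests on a two-group comparison, takes no credit for repeated measures, and presents 312 as the number that offsets attrition.

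**The difference is trivial.** Largely so. Part of the gap of 10 is rounding, since exact 80% power needs about 258. A shift in detectable effect of 0.006 is small beside the planning uncertainty: the same section cites earlier effect sizes from 0.03 to 0.85, and the 20% is itself only an expectation. This bears on the weight of the point, not on whether the figure is right.

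**The 20% could be meant as a share of the final sample.** That reading would give 312, but it is not the usual meaning of an expected attrition rate among participants randomised at baseline.

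**Stronger readings.** A reader might infer that the trial is materially underpowered, or that recruitment has to be raised to 325. The documents support neither. The deficit is about one percentage point of power on the stated calculation, and the planned model may remove it.

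**Conclusion.** The figure is wrong as written, and the consequence is minor. The required 260 is correct. The 312 does not follow from 260 and 20% attrition; 325 does (326 for equal arms). At the plan's own attrition, 312 leaves about 250 participants with week-10 data, with about 79% power for d = 0.35 on the stated two-group calculation.

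The conclusion assumes 1:1 allocation and that 20% is the share of randomised participants lost. The power figure also treats anyone without week-10 data as contributing nothing. That matches the calculation in the Power calculation section but not the planned mixed model, so the power actually achieved remains open.

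Participants with week-10 data should not be called completers here: Other analyses reserves treatment completion for finishing at least five of the eight modules.

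**What to change.** Keep 312 and correct the last sentence of the Power calculation section in one of two ways:

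- *Randomising 312 participants gives about 79% power for an effect size of 0.35 if 20% are lost by week 10*; or
- *Randomising 312 participants allows for 16.7% attrition at 80% power*.

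Add that 325 (326 for equal arms) is the number that would leave 260 after 20% attrition. If the sponsor prefers to rely on the mixed model to justify 312, the section should say so and state the correlation assumed.

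The cost is one sentence. With 312 kept, the abstract and Recruitment need no change, and neither the design nor the analysis is affected. Raising the target to 325 or 326 is possible but is not the cheap option: it means 13 or 14 more participants and a matching change in the abstract and Recruitment.

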### Randomization and blinding

As participants are screened into the study, they will be randomized using a web-based program that was built for this trial. Randomization will be performed within in a permuted block design. The size of the blocks and the exact strata are not revealed in this design paper, so that the underlying algorithm remains unpredictable for the research assistants, but it is stated on the trial registration. This study is single-blind: the research assistants, who will be involved in conducting the clinical interviews after randomization, will be blind to the treatment condition and the participants will be asked not to reveal their treatment condition during the interview. Research assistants who perform the assessments are not involved in the intervention process and they will be asked to guess the treatment allocation per participant.

### Analysis

#### Primary analysis

The primary analysis will be conducted on an intent-to-treat basis, including all participants randomized to the study regardless of treatment adherence or attrition or the completion of outcome assessments. The PHQ-9 [30] will serve as the primary outcome measure with the main time point of effectiveness at post intervention (10 weeks from baseline). Prior to the effect analyses the baseline comparability of the two groups in terms of prognostic variable distributions will be checked. If, despite randomization important differences exist, these variables will be adjusted for in the analyses by their inclusion as covariates.

Each repeated outcome measure will be analyzed as a dependent variable using linear mixed models for fixed (treatment) and random effects models (participant) for independent variables. These models are superior for the analysis of longitudinally correlated data (within subjects) and can optimally deal with missing values, i.e. they prevent complete-case bias by incorporating all available data. In these analyses, a treatment × time interaction term will represent the effect of the intervention on the change of the outcome variable over time. Effect modification of treatment by potential moderators will be studied by including interaction terms of treatment times the moderator variable and testing their statistical significance. Potential mediation of the effect of treatment will be studied using the mediation model proposed by Preacher and Hayes [46]. All effects parameters will be supplied with a 95 % confidence interval. The two-sided significance level will be set at *p* = 0.05.

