#### Primary outcome

The primary outcome is self-reported depressive symptoms based on the Patient Health Questionnaire-9 (PHQ-9) [30] at post intervention (10 weeks from baseline). However, overall during the study, it will be administered at baseline, post intervention (10 weeks from baseline), follow-ups (3 months and 6 months from baseline), as well as biweekly during the 8-week intervention period.

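### Covariates enter the primary model only if an undefined baseline check finds imbalance; baseline PHQ-9 and the randomisation strata should be fixed in the model in advance

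*Protocol article*

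**What the plan says.** The Primary analysis section has one rule for covariates, in two steps. First: "Prior to the effect analyses the baseline comparability of the two groups in terms of prognostic variable distributions will be checked". Then: "If, despite randomization important differences exist, these variables will be adjusted for in the analyses by their inclusion as covariates". It does not say what makes a difference important, which variables are candidates, or that any covariate is included whatever the check shows.

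The same section specifies a linear mixed model for each repeated outcome, with treatment as a fixed effect and participant as a random effect. The effect of interest is that a "treatment × time interaction term will represent the effect of the intervention on the change of the outcome variable over time". The Primary outcome section says of the PHQ-9 that "it will be administered at baseline, post intervention (10 weeks from baseline), follow-ups (3 months and 6 months from baseline"), and also biweekly during treatment.

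The Randomization and blinding section describes permuted blocks and states: "The size of the blocks and the exact strata are not revealed in this design paper". Strata therefore exist, are deliberately withheld, and are said to be on the registration. The Other analyses section uses a similar imbalance-driven rule for the completers.

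**The concern.** The rule lets the observed arms decide the primary model. Under randomisation any baseline difference is chance. What adjustment gains depends on how strongly a variable predicts the outcome, not on whether it happens to differ. The rule therefore does two unhelpful things.

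- It may bring in a variable because of a chance difference, with the decision left to judgement because importance is undefined.
- It will usually leave out those variables that belong in the model regardless: the baseline value of the outcome and the factors used to stratify. Stratified randomisation balances the latter by design, so a check for imbalance is very unlikely to select them.

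At stake are precision at no cost in participants, and a primary model that can be written down before the data are seen.

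**Working it through.** **Inputs from the article (Power calculation).** Effect size 0.35, "in a two-sided test at alpha = 0.05", "a power of (1 − beta) = 0.80", two independent groups, 260 evaluable, 20% attrition, 312 randomised.

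**Assumptions, not in the article.** 1:1 allocation; correlation rho between baseline and week-10 PHQ-9 from 0.3 to 0.7; ratio k of baseline SD to week-10 SD; time as categories; complete data at week 10.

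**The plan's own figure.** A two-sample t-test with d = 0.35 needs 130 per arm, 260 in total (power 80.3%). The normal approximation gives 129 per arm, 258 in total. The 260 reproduces, and it uses no baseline information.

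**How often the rule fires (assumed trigger p < 0.05).** One variable: 5%. At least one of m independent variables, 1 − 0.95^m:
- m = 5: 23%
- m = 10: 40%
- m = 15: 54%

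**Reading A: baseline PHQ-9 is the first response.** This is the likely reading. With a random participant effect and time as categories, the week-10 treatment × time contrast is the difference between arms in mean change. In units of the week-10 variance:
- change contrast: 1 + k² − 2·k·rho
- baseline-adjusted: 1 − rho²
- change minus adjusted: (k − rho)², never negative

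With k = 1 the change variance is 2(1 − rho), and the ratio of adjusted to change is (1 + rho)/2. The effective effect size is 0.35 divided by the square root of the variance. For rho = 0.3: 0.35/√1.4 = 0.296 for change, 0.35/√0.91 = 0.367 adjusted. Two-sample t-test power with 125 per arm (312 × 0.8 = 249.6, about 250):

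| rho | change | week-10 score only | baseline-adjusted | adjusted minus change |
|---|---|---|---|---|
| 0.3 | 64.4% | 78.7% | 82.4% | 18.0 |
| 0.4 | 71.1% | 78.7% | 85.3% | 14.2 |
| 0.5 | 78.7% | 78.7% | 88.9% | 10.2 |
| 0.6 | 86.9% | 78.7% | 93.1% | 6.2 |
| 0.7 | 94.5% | 78.7% | 97.1% | 2.6 |

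At the stated 260 evaluable (normal approximation) the pattern is the same: change 66.5%, 80.6%, 88.4% and 95.4% against adjusted 84.1%, 90.3%, 94.1% and 97.7% at rho 0.3, 0.5, 0.6 and 0.7.

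**Unequal SDs.** Entry requires a PHQ-9 of at least 10, which may narrow the baseline SD. Adjusted power is unchanged; the change contrast improves (125 per arm):

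| k | change at rho 0.3 / 0.4 / 0.5 | gain from adjusting (points) |
|---|---|---|
| 0.8 | 73 / 79 / 85% | 10 / 7 / 4 |
| 0.7 | 76 / 82 / 87% | 6 / 4 / 2 |
| 0.6 | 79 / 84 / 89% | 4 / 2 / 0 |

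At rho 0.6 and 0.7 the gain is below 2 points for all three ratios.

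**Reading B: baseline is not in the response, and the rule decides.** Simulation of a week-10 comparison, 260 evaluable, equal SDs, 15,000 runs per setting, trigger p < 0.05 on baseline PHQ-9:

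| rho | adjust if imbalanced | always adjust | type I error of the rule |
|---|---|---|---|
| 0.3 | 80.7% | 83.4% | 5.1% |
| 0.5 | 81.5% | 90.5% | 4.3% |
| 0.6 | 81.6% | 93.9% | 4.1% |
| 0.7 | 82.6% | 97.5% | 3.5% |

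The trigger fires in about 5% of runs, so most of the gain is lost. Type I error is not inflated.

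**The case against.** Five arguments can be made for the plan.

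- **Baseline PHQ-9 is not thrown away.** This stands on Reading A. A reader might infer that the plan forgoes all the precision in baseline PHQ-9. The article does not support that: the repeated measures start at baseline and the effect is on change. Only the gap between a change contrast and baseline adjustment is lost, and with equal SDs and rho above 0.5 the planned contrast already beats a comparison of week-10 scores alone.
- **The size depends on unstated quantities.** This also stands. A low correlation argued from the entry cut-off sits badly with equal SDs, because the same cut-off narrows the baseline SD. Hence the full range above.
- **The check is harmless to the error rate.** A reader might infer that the arms are unblinded to choose a favourable p-value. The article says only that the check precedes the effect analyses and mentions neither unblinding nor outcome data, and the simulated rule kept its type I error. What remains is discretion, because the trigger is undefined.
- **The check is limited to prognostic variables.** True, but among these the rule still selects by imbalance rather than by prognostic strength.
- **Threshold, variable list and strata belong in the full protocol or analysis plan.** Their absence here is not a fault, and a reader should not infer that the strata are excluded from the model; the article is silent. But the imbalance trigger is stated, not omitted. Defining importance elsewhere would still leave selection by imbalance, and fixing the covariates elsewhere would depart from this text.

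**Conclusion.** The point holds as a badly chosen rule. The primary model's covariates depend on an undefined judgement of chance imbalance, and the rule would seldom select baseline PHQ-9 and almost never the stratification factors.

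On the likely reading, the cost for baseline PHQ-9 is the difference between a change contrast and baseline adjustment: about 18 points of power at rho 0.3 down to about 3 at rho 0.7 with equal SDs, and 0 to 10 points if the baseline SD is 0.6 to 0.8 of the week-10 SD. This rests on d = 0.35, 125 per arm, 1:1 allocation, complete week-10 data, categorical time, and assumed correlations and SDs. The gain from the strata cannot be quantified because they are withheld. The change should be made because it costs nothing, not because the planned analysis is invalid.

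**What to change.** Delete the imbalance rule from the Primary analysis section and put in its place, for example:

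*The primary model includes baseline PHQ-9 and the randomisation stratification factors, fixed in advance and regardless of observed balance. Baseline PHQ-9 enters either as a covariate with a visit interaction, using post-baseline rows only, or as a response with the baseline means of the two arms constrained to be equal. Each secondary scale is analysed in the same way with its own baseline. Baseline tables are descriptive. Adjustment for any variable found to be imbalanced is a sensitivity analysis.*

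One of the two forms for baseline PHQ-9 should be chosen. The strata can be referred to as those used in the randomisation, so their concealment is kept.

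The cost is wording only. Baseline PHQ-9 and the baselines of the secondary scales are already scheduled in Table 1, the strata are known to the randomisation system, and no participants or visits are added.

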Each participant is assigned to a personal lay counselor (supervised by a clinical psychologist) to support the participant in following the online program. Over the course of the program, the lay counselors provide brief feedback online regarding the assignments for each of the eight modules via the online program. In addition, the lay counselors will make brief contact via phone calls to reinforce and encourage participants to work in the online program (weekly during the first 4 weeks and at weeks 6 and 8) in order to enhance adherence to the program and to prevent attrition. The calls do not take more than 20 min each and there is no option for a face-to-face contact.

The GAF-ID program is equipped with a messaging facility that will be used as the main medium of communication between the participants and their lay counselors. The lay counselors log into the GAF-ID program regularly to see the assignments that have been undertaken by the participants and to provide feedback consistent with the BA rationale. If a module has been completed satisfactorily, the lay counselor sends a short message through the GAF-ID program with feedback on the previous module and encourages the participants to engage in the next module. If the participants cannot finish the assignments or seem to not understand the instructions, they can send a message to their lay counselors, and the lay counselors will provide assistance. Further, the lay counselors can see the log-in history of the participants they have assisted, and can send reminders via email and text message to those participants who do not log in to the program each week. Phone calls will follow if the participant fails to reinitiate the intervention after one more week.

All lay counselors will work under the supervision of licensed clinical psychologists and regularly report on the participant’s progress to them as their supervisors. The lay counselors present their cases to their supervisors and address concerns in regular weekly supervision.

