### Support

#### Lay counselors

We plan to recruit 20–30 persons to serve as lay counselors for this study. Our lay counselors meet the following criteria: (1) age between 20 and 40 years with no restriction on gender, (2) minimum senior high school education, (3) willing to participate fully during the trial process, (4) no professional background as a mental health specialist, and (5) willing to participate in the training for lay counselor in this study.

The focus of the lay counselors’ support is to help each participant follow the GAF-ID program by (1) explaining to the participants how GAF-ID works, (2) providing technical assistance for participants, (3) providing short feedback to each of the completed modules, and (4) reminding participants to complete each online module. The lay counselors will not provide any additional counseling.

All lay counselors receive 2 days of intensive training during which all features of the Internet-based BA are discussed and role-plays are conducted. Other technical issues addressed during the training include how to handle technical problems that may arise, how to handle participants with low motivation, and how to monitor suicidality or other serious deteriorations during the intervention. They will receive printed training modules to help them do their tasks during the trial.

To promote treatment integrity and consistency, we provided, apart from the 2 days of training, a treatment guidance protocol, a weekly structured support checklist, a participant’s short progress report template, and regular supervision by a clinical psychologist. In order to elicit and to monitor adherence, the lay counselors will fill out a weekly structured checklist on the support that they have given to each participant. To assure integrity and consistency further, the lay counselors will also be asked to write a regular short progress report on each participant. They will give both the checklist and the report to the clinical psychologists who supervised them. The clinical psychologists will then provide necessary feedback and consultations.

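### GAF-ID participants are nested in 20–30 lay counselors and PE participants in none; the primary model and the power calculation ignore this, which matters if the counselor ICC is above zero

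*Protocol article*

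**What the plan says.** All references are to the protocol article.

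- **Intervention: Guided Act and Feel Indonesia (GAF-ID).** "Each participant is assigned to a personal lay counselor (supervised by a clinical psychologist"). The counselor comments on the assignments of all eight modules, makes scheduled calls (weekly for the first four weeks, then at weeks 6 and 8), and follows up those who stop logging in.
- **Lay counselors.** The plan is for 20–30 "persons to serve as lay counselors for this study". They have no professional mental health background and receive two days of training.
- **Control condition.** PE participants get no support from counselors or psychologists.
- **Power calculation.** "The power is calculated to detect differences between two independent groups". The inputs are a standardised effect of 0.35, a 5% two-sided significance level and 80% power. They lead to 260 evaluable participants, raised to 312 for 20% attrition. No design effect or ICC appears.
- **Primary analysis.** Repeated outcomes are analysed with "linear mixed models for fixed (treatment) and random effects models (participant) for independent variables". The reason given is correlation within subjects over time. Counselor is not mentioned here or in any other analysis section.

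**The concern.** This is a partially nested design: one arm is grouped by the person who delivers the support and the other is not. Participants who share a counselor may have outcomes more alike than participants who do not. A participant random effect handles repeated measures on one person. It does nothing for similarity between people who share a counselor.

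If such similarity exists, the GAF-ID mean is less precise than the model reports. The confidence interval is then too narrow, and the error runs towards declaring GAF-ID superior. A counselor effect is plausible: the counselors are briefly trained lay people, their calls are meant to improve adherence and limit attrition, and the protocol itself adds checklists, progress reports and supervision to keep delivery consistent.

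**Working it through.** **Inputs from the protocol article.** Effect size 0.35 (SD = 1), two-sided alpha 0.05, power 0.80, 260 evaluable, 312 randomized, 20% attrition, J = 20 to 30 counselors.

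**Assumptions.** 1:1 allocation (no ratio is stated), equal attrition in both arms, equal caseloads, total SD of 1 in each arm, and a counselor ICC of 0 to 0.10. As in the plan's own calculation, the week-10 comparison is treated as a comparison of two means.

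**Step 1: reproduce the plan's figure.** The two-sample t-test needs 130 per arm, 260 in total, with power 0.803. The normal approximation gives 129 per arm, 258 in total. The stated 260 is therefore right, but only under full independence.

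**Step 2: evaluable number after attrition.** 312 × 0.8 = 249.6, about 125 per arm. Without any clustering, power = Φ(0.35/√(2/125) − 1.96) = Φ(2.767 − 1.96) = 0.790. This one-point gap from 80% arises because 260 was multiplied by 1.2 instead of divided by 0.8 (260/0.8 = 325). It has nothing to do with counselors and must be kept apart from the clustering effect.

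**Step 3: cluster size.** m = 125/J: 125/30 = 4.2 to 125/20 = 6.3 (6.25 unrounded).

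**Step 4: formulas.**
- Design effect in GAF-ID: DE = 1 + (m − 1) × ICC
- True SE = √((DE + 1)/125); SE from the stated model = √(2/125)
- SE ratio R = √((1 + DE)/2)
- True type I error = 2 × (1 − Φ(1.96/R))
- Power when correctly analysed = Φ(0.35/true SE − 1.96)

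**Step 5: worked case, ICC 0.05.**
- J = 20: DE = 1 + 5.25 × 0.05 = 1.2625; R = √1.131 = 1.064; type I error = 2 × (1 − Φ(1.843)) = 6.5%; true SE = √(2.2625/125) = 0.1345; power = Φ(2.601 − 1.96) = 73.9%.
- J = 30: DE = 1 + 3.167 × 0.05 = 1.158; R = 1.039; type I error = 5.9%; power = 75.9%.

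**Step 6: full range, J = 30 to J = 20.**

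| Counselor ICC (assumed) | SE too small by a factor of | True type I error | Power |
|---|---|---|---|
| 0 | 1.00 | 5.0% | 79% |
| 0.01 | 1.01 | 5.2–5.3% | 78% |
| 0.02 | 1.02–1.03 | 5.4–5.6% | 77–78% |
| 0.05 | 1.04–1.06 | 5.9–6.5% | 74–76% |
| 0.10 | 1.08–1.12 | 6.9–8.1% | 69–73% |

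Against the 79.0% baseline, clustering alone costs about 1–2 points at ICC 0.02, 3–5 at 0.05 and 6–10 at 0.10. Satterthwaite degrees of freedom take off roughly one further point.

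**Step 7: sensitivity to the evaluable number.** With the planned 130 per arm, ICC 0.05 gives a type I error of 6.0–6.6% and power of 75–77%. The picture is the same.

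**The case against.** **The ICC may be negligible.** Support is structured: fixed modules, calls of at most 20 minutes, no face-to-face contact, no counseling beyond the program, checklists and weekly supervision. Nesting alone does not prove correlation, and at ICC 0.01 the type I error is only 5.2–5.3%. This stands as a limit on size. It makes a small ICC plausible but does not make it zero, and the trial cannot show that it is small unless counselor is modelled.

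**Type I inflation needs a particular null.** If the program and its support changed nothing for anyone, counselors would create no variance and no inflation. The excess error arises when the average effect is zero but counselors differ. This stands too, and is a further reason for conditional wording.

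**A further random term could be in the SAP.** The article does not say that participant is the sole random effect. But it does more than leave the matter open: it names the random effect, ties it to within-subject correlation, and bases the power on independent groups. A change to a stated method is being asked for, not missing detail.

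**Readings that go too far.**
- A reader might infer that the primary interval is certainly too narrow. The article gives no ICC, so this holds only if the ICC is above zero.
- A reader might take cluster size from 156 randomized per arm (5.2–7.8 per counselor) and power from 125 evaluable. That mixes two sample sizes and overstates the loss. With 156 used for both, ICC 0.05 gives a type I error of 6.2–7.0% but power of about 82–84%.
- A reader might infer that the trial sets out to draw conclusions about lay counselors in general. The stated aim is to compare GAF-ID with PE; wider use is a hope in the Discussion, not an objective.

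**Conclusion.** The point holds in conditional form. The article describes one-arm nesting, yet it specifies an analysis and a power calculation that leave it out. For any positive counselor ICC the direction is fixed: standard error too small, type I error above 5%, power below that stated. The size rests on an assumed ICC, 1:1 allocation and even caseloads. It is small at ICC 0.01–0.02 and material from about 0.05. The shortfall from 80% to 79% at ICC 0 belongs to the attrition arithmetic and should not be counted as a clustering loss. A possible further level, the 10–15 psychologists who supervise the counselors, is not quantified here. This is a change that should be made, but it does not undermine the design.

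**What to change.** 1. **Primary analysis:** add a counselor random effect that applies to the GAF-ID arm only, with each PE participant as their own cluster. Allow a separate residual variance in each arm, and use Satterthwaite or Kenward-Roger degrees of freedom.
2. **Fallback:** with only about 4–6 evaluable participants per counselor, the counselor variance may be estimated at zero or the model may not converge. State in advance what happens then, for example cluster-robust standard errors with a small-sample correction.
3. **Data and reporting:** keep counselor ID in the analysis data set and report the counselor ICC.
4. **Power calculation:** state that the figure assumes no counselor clustering, and give the range in the table above, including the ICC 0 line.

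The cost is one model term and an identifier that should already exist from the assignment of counselors. The downside is a slightly wider confidence interval and a less favourable stated power. Sample size, recruitment and treatment stay as they are.
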